#### 2.2.2. Data Analysis of the Pilot Study

Data will be analysed using descriptive and exploratory inferential statistics using SPSS 26.0 with the intention of feasibility assessment and not for formal hypothesis testing [70]. In a single-group pre-post-test study, the characteristics of the sample will be summarised using descriptive statistics such as frequency counts, percentages, means, and standard deviations. The descriptive data analysis can give an overview of the sample’s age, gender, ethnicity, education level, income, breast cancer treatments, and other demographic variables.

The feasibility outcomes of the study such as recruitment, follow-up assessments, and questionnaire/intervention acceptability will be determined using descriptive data [71]. Mean and standard deviation will be used to analyse interval and ratio data, such as the time taken for participant recruitment and the average time and frequency of physical activity [71]. The acceptability of the questionnaires will be determined by calculating the proportion of missing data [71]. The feedback on the intervention is measured by assessing the participants’ satisfaction scores. Any adverse events related to physical activity, such as musculoskeletal aches and pain, dizziness, and falls, will be presented as the absolute number of events and the total percentage.

Secondary clinical and behavioural outcomes will be presented descriptively at each assessment point to evaluate the feasibility outcomes for future randomization [70]. Changes over time will be explored using non-parametric methods, given the small sample size and single-group pre–post design [71,72]. The Friedman test will be conducted for continuous variables to correlate the data at three different time points [73]. Cochran’s Q test will be utilised for categorical variables to assess changes in proportions between the pre-test and post-test assessments [74]. These analyses will be exploratory only and will not be interpreted as formal hypothesis tests. Analyses will be conducted using available data from participants who complete each assessment. The extent and reasons for missing data will be reported. Participant attrition will be monitored throughout the study, and differences between completers and non-completers will be examined to evaluate potential attrition bias. No imputation of missing data is planned due to the small sample size and feasibility focus of this study.

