Our team has previously conducted two systematic reviews to synthesise the existing evidence of self-managed non-pharmacological interventions for BCSs [34] and CVDs [35]. The reviews identified common non-pharmacological interventions for BCSs and CVDs, which could guide the selection and development of an evidence-based non-pharmacological intervention programme for BCSs with CVDs in this research project. Managing two complex health conditions, BC and CVD simultaneously presents distinct challenges such as clinical and system-level challenges that may influence how patients respond to or benefit from self-managed non-pharmacological interventions. Clinical challenges such as shared modifiable and non-modifiable risk factors, cardiotoxic effects of cancer treatments, and poor cancer outcomes due to CVD, and system-level challenges such as poor integration of cardio-oncology services, lack of coordination between specialties, absence of a shared care model and limited awareness among clinicians about cardiotoxicity complicate the long-term surveillance of BCSs [4,28,36,37]. Considering these challenges and the elevated risk for CVDs, this highlights an urgent need for tailored, evidence-based self-management interventions delivered within primary healthcare.

This research project was thus proposed to develop a nurse-led and GP-supported self-management (NGPS) intervention for BCSs with CVDs and evaluate its feasibility and potential effects in primary care settings with the following specific objectives: (1) To develop an evidence based NGPS intervention protocol that is tailored to the needs of BCS with CVDs; (2) To examine the feasibility, acceptability, and safety of the NGPS intervention in BCS with CVDs; (3) To test the preliminary effects of the NGPS intervention on cardiovascular health outcomes, such as physiological outcomes, behavioural outcomes including dietary intake, physical activities and smoking, psychosocial outcomes including self-efficacy, QoL, anxiety and depression, and healthcare usage, in BCS with CVDs; (4) To explore the experiences of patients and healthcare professionals who participate in this pilot study and to identify any barriers and facilitators in the implementation of the NGPS intervention in Australian primary care settings; and (5) To refine the NGPS protocol based on the results of this pilot trial and the qualitative process evaluation.

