#### 2.2.1. Outcomes and Measurements

The study will employ a demographic data sheet that has been specifically developed by the research team to gather information on the socio-demographic characteristics of the patients, such as age, height, race/ethnicity, as well as their medical history, such as date of BC and CVD diagnosis, the current stage of BC, the type and date of BC and CVD treatment.

(1)Primary outcomes

The primary outcomes will be the feasibility, acceptability and safety outcomes. The feasibility outcome will measure the feasibility of the questionnaires, recruitment and the intervention delivery. The acceptability of the intervention will be assessed by assessing the acceptability among the participants. The safety of the intervention will be measured by the safe delivery of the intervention. The primary outcome will also measure the recruitment, retention, and dropout and will be evaluated as the fundamental aim.

The recruitment rate is the percentage of eligible participants who consented to participate in the study.The retention rate will measure the percentage of participants who remain in the study throughout the entire study period, from enrolment to follow-up (week 12).The dropout rate will be calculated based on the percentage of participants withdrawn from the study after enrolment.The feasibility of the questionnaires will be assessed by measuring the percentage of missing responses for each item and the entire scale.The feasibility of the recruitment will be assessed by measuring the number of weeks or months needed to achieve the target number of sample size.The adherence rate to the NGPS protocol will measure the percentage of participants who followed the interventions as intended. This will measure the feasibility and acceptability of the study intervention.The safety of the intervention includes discomfort or adverse effects related to NGPS intervention by keeping a daily logbook and reporting via telephone or face-to-face.Acceptability will assess the participant’s satisfaction, benefits received and obstacles faced using an investigator-created questionnaire.

(2)Secondary outcomes

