#### 2.2.3. Quality Assurance and Intervention Fidelity

To ensure the quality assurance of the pilot study, the primary researcher will create standard operating procedures for all study procedures, including recruitment and data collection. Participant recruitment will be conducted using inclusion and exclusion criteria, following recruitment procedures detailed in the study protocol, and all recruitment activities will be documented, monitored, and reported at the biweekly research meetings. Data collection will be conducted by the primary researcher who is completely aware of the data collection procedures to ensure standardisation, and the data will be collected at the time points mentioned to ensure quality.

To ensure intervention fidelity, interventions from an intervention strategy pool (the intervention strategy pool will be developed and validated after the qualitative interviews) will be used for standardisation and to avoid variability in the delivery. The researchers will maintain a study activity log, including intervention delivery and any deviations from the protocol. These details will be reported at the biweekly research meetings. Any decisions on altering the study protocol will be discussed between the researchers and a letter of variation will be submitted to the University of Southern Queensland Human Research Ethics Committee, stating the changes and obtaining final approval. Additionally, the primary researcher will obtain feedback from the patients and the healthcare providers through qualitative process evaluation (as described in Section 2.3) on various components of the NGPS intervention such as relevance, accuracy and wording of the intervention protocol to ensure all components are delivered as intended.

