## Figures and Tables

**Figure 1 nursrep-16-00253-f001:**
[figure not shown]
Overall research design.

**Table 1 nursrep-16-00253-t001:** Self-management non-pharmacological interventions for CVDs.

Condition	Non-Pharmacological Interventions
CVDs	Diet, physical activity, smoking cessation and weight management
Coronary heart disease	Diet, physical activity, smoking cessation and weight management
Heart failure	Diet and physical activity
Atrial fibrillation	Weight loss and exercise recommended to avoid intensive endurance training
Stroke	Diet, physical activity, smoking cessation, weight management and decreased alcohol consumption and mental health interventions such as mind–body exercise such as taichi, yoga and qigong for mental health management
Peripheral artery disease	Physical activity and smoking cessation
Hypertrophic cardiomyopathy	Moderate to low degree recreational activity and achieve or maintain weight loss for obese individuals

The information presented in this table was adapted from the systematic review [35].

**Table 2 nursrep-16-00253-t002:** Self-management non-pharmacological interventions for BCSs.

Condition	Non-Pharmacological Interventions
Anxiety, depression and distress	Meditation, massage therapy, passive music therapy and hypnosis. Self-administered cognitive behavioural stress management for the management of anxiety and progressive muscle relaxation, guided imagery, visualisation techniques, and autogenic training) for depression management
Fatigue	Physical activity, yoga and hypnosis
Pain	Physical therapy, music therapy post-surgery and hypnosis
Breast cancer-related lymphedema	Progressive resistance training, aerobic exercises, aquatic exercises, self-massage, diaphragmatic breathing and weight reduction
Nausea and vomiting	Self-acupressure and relaxation
Neuropathy	Physical activity
Sleep improvement	Yoga
Vasomotor/hot flushes	Physical activity
Quality of life improvement	Regular exercise or sports, meditation, yoga and hypnosis
Reduction in risk of recurrence	Physical activity, exercise and weight management
Health promotion	Weight management, physical activity, nutrition, alcohol limitation, and smoking cessation

The information presented in this table was adapted from the systematic review [34].

**Table 3 nursrep-16-00253-t003:** A preliminary NGPS intervention protocol.

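### The primary safety outcome covers the whole NGPS intervention, but the only adverse-event analysis sentence covers events related to physical activity

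*Protocol article*

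**What the plan says.** Objective 2 in the Introduction of the protocol article is "To examine the feasibility, acceptability, and safety of the NGPS intervention in BCS with CVDs". Section 2.2.1 repeats this at outcome level: "The primary outcomes will be the feasibility, acceptability and safety outcomes". It then gives the content of the safety outcome and how it is recorded: "The safety of the intervention includes discomfort or adverse effects related to NGPS intervention by keeping a daily logbook", with reporting by telephone or face to face. The reference in each case is the intervention, with no restriction to one component.

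Section 2.2.2 has one sentence on adverse events. Its subject is "Any adverse events related to physical activity, such as musculoskeletal aches and pain, dizziness, and falls", and these "will be presented as the absolute number of events and the total percentage".

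The intervention is wider than exercise. Table 1 lists, for cardiovascular disease, "Diet, physical activity, smoking cessation and weight management". Table 2, for breast cancer survivors, includes "Meditation, massage therapy, passive music therapy and hypnosis" among other strategies. Under Table 3 the nurse builds a personal care plan from a strategy pool. According to Section 2.2.3, "the intervention strategy pool will be developed and validated after the qualitative interviews".

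**The concern.** A primary outcome and its analysis should cover the same events. Here the analysis sentence takes a subset of the outcome. A participant whose plan is mainly dietary or mind-body could report an intervention-related effect in her logbook, and the written plan would give no instruction to summarise it. An analyst who follows Section 2.2.2 literally would present an exercise-related count as the safety result of a multi-component intervention, and so under-report a primary outcome.

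A second, smaller difficulty lies in the summary measure. The sentence promises a count of events and a percentage but does not say of what. It could be a percentage of participants or of events. With daily logging, repeated entries from one person can be confused with several people affected.

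**Working it through.** This is mainly a comparison of texts. The arithmetic plays a supporting part.

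**1. Scope of outcome against scope of analysis (protocol article).**

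| Element | Place | Events covered |
|---|---|---|
| Objective 2 | Section 1 | Safety of the NGPS intervention |
| Outcome definition | Section 2.2.1 | Discomfort and adverse effects related to NGPS |
| Data collection | Section 2.2.1 | The same, by daily logbook and by phone or face-to-face report |
| Analysis | Section 2.2.2 | Adverse events related to physical activity |

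The first three rows agree and the fourth is narrower. The examples in Section 2.2.2 (aches and pain, dizziness, falls) form an open list, but they illustrate the physical-activity class and do not extend it to other components.

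**2. What is left without a stated summary.** Divide the events by two questions: is the event related to NGPS, and is it related to physical activity?

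- NGPS-related and tied to physical activity: in the outcome and in the analysis sentence. No gap.
- NGPS-related but tied to another strategy: in the outcome, with no stated analysis. This is the gap.
- Not related to NGPS: outside the outcome as Section 2.2.1 defines it. The mismatch does not cause its absence.

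**3. Is the second group empty?** Not on the present text. Tables 1 and 2 put diet, smoking cessation, weight management, massage, hypnosis and others among the candidate strategies. The pool is still to be built, so these are candidates and not settled content. That is also a reason not to tie the safety analysis to one component in advance.

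**4. Can the shortfall be quantified?** Let *f* be the share of NGPS-related events that arise outside physical activity. The reported count is then (1 − *f*) times the full count, and the shortfall is *f*. The documents give no event rates, so any value for *f* is an assumption that simply reappears as the answer. No figure is claimed.

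**5. Sample size and precision.** The plan's figure reproduces: 12 / (1 − 0.20) = 15. With zero events in *n* participants, the exact two-sided 95% upper limit is 1 − 0.025^(1/*n*):

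- *n* = 15: 1 − 0.025^(1/15) = 21.8%
- *n* = 12: 1 − 0.025^(1/12) = 26.5%

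These limits show how little reassurance a zero count gives at this size. They would be the same after the rewording, so they do not measure the defect.

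**6. Denominator.** One affected participant is 1/15 = 6.7% of those recruited, or 1/12 = 8.3% of the evaluable target. If she makes *k* logbook entries for the same complaint, the event count is *k* while the number of persons affected stays at 1. Dividing events by participants would give *k*/15, which is *k* times the proportion affected.

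**The case against.** Section 2.2.2 says that physical-activity events will be presented. It does not say that others will be excluded. The article is a condensed account, and fuller adverse-event tables, including denominators, are commonly left to the full protocol or analysis plan. Collection is not in doubt, since the logbook covers all NGPS-related effects. The Discussion states that no progression criteria were set in advance and that findings will be read as preliminary and descriptive, so no decision turns on the count.

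Most of this stands, and it limits the weight of the point. It does not remove it. The article does fix an adverse-event summary, and the class it names is narrower than the primary outcome defined one section earlier. That is an inconsistency in the text and not a detail left for later. The denominator alone would not merit a comment, but it belongs in the same sentence and can be settled with it.

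Stronger readings are tempting, and the documents do not support them:

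- *Cardiovascular events fall outside the safety result.* Those tied to physical activity fall within the open list, and those unrelated to NGPS are outside the outcome by definition. Cardiovascular hospital and GP attendances are also counted under healthcare usage, a secondary outcome. Only NGPS-related cardiovascular events not tied to physical activity share the gap.
- *Restricting to related events is itself an error.* It is how Section 2.2.1 defines the outcome. All-cause reporting may be preferable in a single-arm study, but its absence is not a contradiction.
- *The logbook stops at week four.* The article gives no end date, so neither a maximum number of entries nor a need to extend the logbook can be inferred.

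**Conclusion.** The point holds as a mismatch of scope. Section 2.2.2 analyses part of the primary safety outcome that Section 2.2.1 defines, and NGPS-related effects of non-exercise strategies have no stated place in the result. The conclusion rests on two readings: that the sentence in Section 2.2.2 is the whole of the stated adverse-event analysis, which is true of the article, and that at least one non-exercise strategy will enter the final pool, which Tables 1 and 2 make likely but do not settle. The number of events affected is unknown and could be small. The mismatch should be corrected before the pilot, but it does not undermine the study: the data would be collected anyway, no progression rule depends on the count, and the article already describes its findings as preliminary.

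**What to change.** Reword the adverse-event sentence in Section 2.2.2 along these lines: all discomfort and adverse effects related to the NGPS intervention, as defined in Section 2.2.1, will be summarised as the number of events and as the number and percentage of enrolled participants with at least one event; events related to physical activity will be shown as a subset.

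An optional addition is to list every recorded event whatever its judged relation to NGPS, with relatedness shown descriptively. If this is adopted, the definition in Section 2.2.1 must be changed as well. Otherwise one mismatch replaces another.

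The cost is a sentence of protocol wording and some extra tabulation. The core change needs no new data collection and leaves the sample size as it is. The reported event figures may look slightly less favourable because more of the defined outcome is counted.

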### 2.2. Phase II: The Pilot Study and the Qualitative Process Evaluation

Study design of the pilot study

In phase II, the newly developed intervention protocol’s feasibility and acceptability will be tested using a pre-post pilot study incorporating a qualitative process evaluation.

(1)Pilot study: Study sample

The inclusion criteria will be female patients (1) aged 18 years or older; (2) confirmed diagnosis of breast cancer at stage I, II, or IIIa; (3) confirmed diagnosis of CVDs, such as heart failure, hypertension, coronary artery disease, cerebrovascular accidents (e.g., stroke, transient ischemic attack), cardiomyopathy and arrhythmias; (4) able to read, write, and communicate in English; (5) have completed active anticancer treatment including chemotherapy and radiotherapy, and are receiving regular healthcare in primary care centre from GP/practice nurses; (6) willing to participate in the research study and provide informed consent. The exclusion criteria: patients with unstable health conditions with mental health issues or critically ill patients unable to participate in physical activities (e.g., suffering from life-threatening diseases, extremely weak), cognitive impairment, currently involved in another research study, or scheduled anticancer treatment during the study period.

(2)Sample size and study settings

Based on the rule of thumb suggested by Julious [60], a sample size of 12 will be employed in this pilot single-group pre-post study. When taking into account a 20% dropout rate based on a clinical study by Cramer et al. [61], 15 participants will be recruited for this study.

(3)Study procedure

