Potential participants will be identified and approached in collaboration with the primary care centres and the healthcare professionals. The participants will be informed of the study by the treating doctor or the centre by using flyers or through emails sent by the centre reception. The healthcare professionals at the centre will be introduced to the study through meetings, presentations or brochures to help with the recruitment and to distribute the participant information sheet. The interested participants will contact the primary researcher. Prior to recruitment, potential participants will be screened for eligibility, and informed consent will be obtained from eligible participants after explaining the study’s purpose, procedures, and risks. Participants will be advised to continue receiving usual care from their medical centre during the study.

The planned data collection will be taking place at three points during the study: at the beginning of the study before the intervention (T1). At week four immediately after the NGPS intervention (T2) and at week 12, which is eight weeks post-intervention (T3). The eight-week follow-up is based on previous research suggesting that it typically takes around eight weeks for individuals to change a habit or behaviour [62]. The interventions will be carried out through a combination of telehealth and in-person consultations, with alternating durations depending on the session type.

A qualitative process evaluation will be conducted at the end of the intervention, at week four by using semi-structured interviews. All the participants will be invited to participate in the qualitative interviews.

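### The Friedman test drops participants with a missing visit and gives no size of change; paired within-person change should be the main analysis of the continuous secondary outcomes

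*Protocol article*

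**What the plan says.** **Design (section 2.2).** The target is stated as "a sample size of 12 will be employed in this pilot single-group pre-post study". With a 20% dropout allowance, "15 participants will be recruited for this study". On timing, "The planned data collection will be taking place at three points during the study": baseline (T1), week 4 at the end of the intervention (T2), and week 12 (T3).

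**Analysis (section 2.2.2).**
- Statistics are used "with the intention of feasibility assessment and not for formal hypothesis testing".
- "Secondary clinical and behavioural outcomes will be presented descriptively at each assessment point". Interval and ratio data are summarised by mean and SD.
- For change over time, "The Friedman test will be conducted for continuous variables to correlate the data at three different time points". Cochran's Q is named for categorical variables. Both are declared exploratory.
- On the analysis set, "Analyses will be conducted using available data from participants who complete each assessment".
- On missing data, "No imputation of missing data is planned due to the small sample size and feasibility focus of this study". Amounts of and reasons for missing data will be reported, and completers will be compared with non-completers.

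**Purpose.** Objective 3 in the Introduction concerns preliminary effects on cardiovascular health outcomes. The Abstract says that the secondary outcomes are meant to guide a later, larger trial.

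**The concern.** The article fixes the method for change over time, and three features of that method fit badly with the rest of the section.

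1. **Analysis set.** Friedman needs all three values from each participant, and Cochran's Q has the same requirement. With no imputation, a participant seen at T1 and T2 but not at T3 contributes nothing, although her change over the intervention period was observed. The available-data sentence does not tell the reader this.
2. **Output.** An omnibus rank test says whether the three visits differ somewhere. It does not give the size of the change, its uncertainty, or which visits differ. A test statistic is an odd main tool in a plan that disclaims formal testing and wants preliminary effects.
3. **Description.** The test compares visits. It does not correlate them, as the sentence says.

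At stake is part of the T1-T2 information in a study of 15 people, and the paired estimates most useful for judging preliminary effects. The visit-level summaries fill the gap only partly.

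**Working it through.** **Inputs from the article.** Target 12; dropout 20%; recruited 15; visits T1, T2, T3; no imputation (sections 2.2 and 2.2.2).

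**1. The plan's own figure.** 12 / (1 − 0.20) = 15. It reproduces, and nothing below alters it.

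**2. What Friedman uses under the plan's dropout.** Expected losses are 0.20 × 15 = 3. The article does not say when they occur, so timing is an assumption.
- All 3 leave after T2: 15 T1-T2 pairs are observed, Friedman uses 15 − 3 = 12 participants, and 3 observed pairs are discarded.
- All 3 leave before T2: 12 pairs and 12 complete sets, so nothing observed is discarded.

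The loss is therefore 0 to 3 pairs. An illustrative simulated data set with 3 of 15 lacking T3 confirmed the behaviour. The test returned no result on the incomplete data and ran only on the 12 complete sets.

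**3. If visits are instead missed independently** (assumed probability m at each of T2 and T3): complete sets = 15(1 − m)², T1-T2 pairs = 15(1 − m).

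| m | Complete sets | T1-T2 pairs |
|---|---|---|
| 5% | 13.5 | 14.3 |
| 10% | 12.2 | 13.5 |
| 20% | 9.6 | 12.0 |

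**4. Visit means on changing sets.** Suppose the 3 who leave start d units above the 12 who stay, and nobody changes. The T1 mean on 15 then exceeds the T3 mean on 12 by (3/15) × d = 0.20d. The article gives no value for d. For assumed values of 5, 10 and 15 mmHg in systolic pressure, the apparent fall is 1, 2 and 3 mmHg.

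**5. SD of change from visit SDs.** With equal visit SDs and within-person correlation r, SD of change = visit SD × √(2(1 − r)). The article gives no r.

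| Assumed r | SD of change / visit SD |
|---|---|
| 0.3 | 1.18 |
| 0.5 | 1.00 |
| 0.7 | 0.77 |
| 0.9 | 0.45 |

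The visit SDs alone leave the SD of change uncertain by a factor of about 1.18 / 0.45 = 2.6 over this range.

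**6. Precision of the paired estimate.** The half-width of the 95% CI for a mean change, in SDs of change, is t(0.975, n − 1) / √n. This is 0.64 at n = 12 and 0.55 at n = 15. The 95% CI for an SD at n = 12 runs from 0.71 to 1.70 times the estimate.

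**The case against.** **The available-data sentence can be reconciled with Friedman.** A reader might infer a flat contradiction. The documents do not support that. The sentence can mean data available at each visit, which suits the descriptive tables. It can also mean participants who completed every assessment, or simply observed data without imputation, and both of these suit Friedman. The wording is unclear, not impossible. This objection stands, but the article should still say which participants enter which analysis.

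**The pilot will yield SDs.** A reader might infer that nothing useful for a later trial will be produced. That is wrong, because means and SDs are planned and secondary outcomes are described at each visit. Per-visit SDs and crude differences of means will exist. Only the paired change, its SD and its interval are not named.

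**Attrition is addressed.** Missing-data reporting and a completer versus non-completer comparison are planned, and the latter could reveal the baseline gap in step 4. It does not put the visit summaries on a common set of people.

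**A shortfall below 12 is not established.** The plan's 3 losses leave exactly 12. If each of 15 participants independently has a 20% chance of dropping out, the chance of fewer than 12 complete sets is about 35%. It reaches about 64% only if 5% of the remaining T2 and T3 visits are also assumed missed, a figure that is not in the article.

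**Detail may lie in a fuller document, and the stakes are low.** Pairwise contrasts and intervals are often left to an analysis plan, so their absence alone would be no finding. The point rests on what the article does state: a complete-case omnibus test as the method for change, misdescribed as correlating, beside an available-data sentence. That the outcomes are secondary and exploratory, with feasibility, acceptability and safety primary, lowers the severity. The small sample is a fair reason for rank methods, and a median change with an interval respects it.

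**Conclusion.** The point holds as a moderate to minor one. As written, the change analysis is complete-case. It discards up to 3 observed T1-T2 pairs under the plan's own dropout allowance (all 3 if the losses come after T2), and it returns a p-value where an estimate would serve the stated purpose better. The planned visit summaries do not replace that estimate. They may describe different people at different visits, and they cannot give the SD of change without the within-person correlation. The count of 12 against 15 uses the article's figures plus an assumption about when dropout occurs. The mmHg values, missed-visit rates and correlations are illustrations. No primary outcome and no part of the sample size depends on this.

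**What to change.** In section 2.2.2:

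1. Make the main change analysis for each continuous secondary outcome the within-person change from T1 to T2 and from T1 to T3, using every observed pair. Report the number of pairs, mean change, SD of change and 95% CI. For skewed scores, report the median change with its CI.
2. If Friedman is kept, make it supplementary, label it complete-case, give its n, and say that it compares the three time points. State the complete-case n for Cochran's Q as well.
3. State which participants the available-data sentence covers for the visit summaries, the paired changes and the tests.

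A random-intercept model with visit as a factor is optional. It would use all observed visits but adds distributional assumptions at n = 15.

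The cost is rewording and a little more analysis, with no new data and no change to the 15 recruited. The intervals will be wide (half-width about 0.64 SD of change at n = 12 and 0.55 at n = 15) and should be presented as such.
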